# An innovative case management intervention for people at high risk of permanent work disability to improve rehabilitation coverage and coordination of health services: a randomized controlled trial (AktiFAME, DRKS00024648)

**DOI:** 10.1186/s12913-022-07482-9

**Published:** 2022-03-15

**Keywords:** Case management, Rehabilitation, Disability pension, Randomized controlled trial, Return-to-work, Employment

## Abstract

**Background:**

German social law offers services from various providers and agencies for people with chronic disease or disability. Claiming services requires a high level of information and communication. Dealing with a multitude of actors, such as pension insurance agencies, job centers, employers, physicians, and psychotherapists, and coordinating between and with these actors can delay or prevent the utilization of necessary measures like medical or vocational rehabilitation. We developed a case management intervention for people at high risk of receiving a disability pension to address these challenges.

**Methods/design:**

Our randomized controlled trial tests the effectiveness of the multi-component AktiFAME strategy (Active access, counseling, and case management for people at high risk of permanent work disability). This strategy is comprised of four modules: screening and postal contact, telephone counseling, an initial one-on-one interview, and case management. The randomized controlled trial is complemented by an observational study that exclusively involves the individuals participating in case management and accompanies the implementation of the case management intervention. We enroll 9000 individuals aged 18 to 65 years who were identified as being at increased risk for receiving a disability pension based on administrative data from the German Pension Insurance North but who have not yet applied for rehabilitation. Half of the individuals are randomly assigned to the intervention group and the other half to the control group. The intervention group is contacted and informed about a case management intervention, whereas the control group is not. The primary outcome of the randomized controlled trial is the utilization of rehabilitation services from the German Pension Insurance North (medical or vocational rehabilitation). Data on rehabilitation will be provided by the German Pension Insurance North 1 year after random allocation. Secondary and tertiary outcomes cover additional administrative data (e.g., employment and welfare benefits) and a range of patient-reported outcome measures.

**Discussion:**

This randomized controlled trial is designed to determine the effectiveness of a newly implemented multi-component strategy to promote participation and rehabilitation coverage among individuals at high risk of receiving a disability pension.

**Trial registration:**

German Clinical Trials Register (DRKS00024648, April 27, 2021).

**Supplementary Information:**

The online version contains supplementary material available at 10.1186/s12913-022-07482-9.

## Background

Employment is a key resource for participation in society [1–3]. It ensures income and material security, supports an independent lifestyle, and reduces the risk of poverty in old age by building up pension entitlements. Employment enables social contacts and experiences of self-efficacy, and it can give a sense of purpose and contribution [4]. If people become chronically ill (e.g., due to mental illness), this may jeopardize staying at work and future work participation. In case of long-term and presumably permanent work disability, a disability pension can be granted to reduce income losses. Disability pensions are usually granted for a limited period. After 9 years, they are converted into permanent pensions. Currently, more than 1.8 million people in Germany are receiving a disability pension. Every year, about 350,000 applications for a disability pension are received. Slightly more than half of the completed cases are approved. Despite the high absolute number of disability pensions in Germany, the average individual risk of receiving a disability pension is low: four to five out of every 1000 actively insured persons (i.e., persons who are entitled to a pension on the basis of previous employment and associated social security contributions) start a disability pension each year [5]. The 5-year incidence is just under 2% [6]. Expenditure on disability pensions annually is about 21 billion euros. In 2020, 175,808 people were registered as starting to receive a disability pension, of whom 84,640 were men and 91,168 were women. The average age of retirement was around 53 (i.e., about 14 years before the standard retirement age) [7]. The most important health problem for the granting of a disability pension is mental illness, accounting for about 42% of all new disability pensions, followed by cancer and musculoskeletal disorders [5].

According to Article 27 of the Convention on the Rights of Persons with Disabilities [2], persons with disabilities have “the right to the opportunity to gain a living by work freely chosen or accepted in a labor market and work environment that is open, inclusive and accessible to persons with disabilities”. Earning a living through employment requires assistance in the transition to the general labor market and the promotion of job re-entry for people with disabilities. The range of supporting services provided for this purpose under German social law is broad (e.g., medical rehabilitation, retraining, or job adjustments). Frequently, several of these services are needed to enable people to stay at work or return to work. Different service providers may be involved, such as pension insurance, job centers, the employment agency, social welfare institutions, and health insurance agencies. Employers, occupational health physicians, general practitioners, and psychotherapists are also important players. Moreover, it is often not clear to whom a person has to turn in order to apply for services. To meet these challenges, coordinating and accompanying interventions have been proposed and implemented in recent years [8]. In a systematic review of the effects of coordinating return-to-work interventions, 14 randomized controlled trials with 12,568 employees were summarized [9]. The people included in these studies had musculoskeletal or mental health problems and were on sick leave for at least 4 weeks. The authors of that review did not find any benefits for returning to work in favor of the interventions considered. Although small effects were reported for patient-reported outcomes (e.g., pain and functional capacity), the differences were not clinically significant. The quality of the evidence was considered low due to the risk of bias and the low precision of the effect estimators. The transferability of these results to the support of individuals at high risk of permanent exit from work is, however, severely limited as the included populations had rather low levels of sickness absence (i.e., at least 4 weeks of sickness absence), and the interventions were very heterogeneous. A recent randomized controlled trial from Denmark, accompanied by a very rigorous process evaluation, demonstrated higher return-to-work rates in favor of the intervention group when reaching people that had an obvious need for coordinated support [10].

In our study, we take the return-to-work coordination programs described above and develop them into a multi-component strategy. Our strategy is comprised of four modules: screening of administrative data and postal contact, telephone counseling, an initial one-on-one interview, and a case management intervention. We expect this complex intervention to provide people at high risk of receiving a disability pension with the tailored support they need to sustain their work ability and work participation.

### Objectives

We designed a randomized controlled trial to clarify if our strategy increases the likelihood to apply for rehabilitation services and improves several secondary and tertiary outcomes compared to the usual approach, where people with chronic diseases and disabilities have to coordinate their services themselves. An observational study was nested to assess how well the case management intervention is implemented.

### Trial design

Our study is a randomized controlled trial with two parallel groups with a nested observation study. For our randomized controlled trial, we use an approach proposed by Zelen [11]. After identifying 9000 persons with an increased risk of receiving a disability pension, these individuals are randomly assigned to an intervention group or a control group. Only the intervention group is informed about the possibility of our case management intervention. The superiority of our multi-component strategy will be tested primarily with administratively available data provided by the German Pension Insurance North. These data constitute our primary and secondary outcomes. This allows a pragmatic population-based randomized controlled trial. A similar approach was adopted in the evaluation of other population-based screening programs [12, 13]. Our comparator reflects the current practice whereby people with chronic conditions must first apply for rehabilitation but are not consistently and comprehensively informed in advance by the pension insurance about the options to support their participation. In addition, all individuals will be contacted by the German Pension Insurance North 1 year after random assignment, informed about the study and asked to participate in a postal survey to assess several tertiary outcomes. Moreover, the implementation of the case management is accompanied by an observational study that exclusively includes the individuals participating in the case management intervention.

## Methods

### Study setting

Our intervention is implemented in 206 postal code districts in the German states of Schleswig-Holstein and Mecklenburg-Vorpommern and overseen by seven regional case managers. Outreach contacts usually take place in the home environment of the participants.

### Eligibility criteria

We include persons aged 18 to 65 years who received sickness benefits in the previous year and were at increased risk of receiving a disability pension as indicated by a standardized and validated risk index [6]. All included persons have received at least 180 days of social security contributions from employment or unemployment benefits or sickness benefits in the previous year.

We exclude individuals who have used rehabilitation services in the past 3 years or already receive a disability pension. Some people may be identified as having a high risk of permanent work disability although our case management intervention is not appropriate, e.g., if people require medical care due to an acute illness or need support due to an addiction disorder. We will inform these people about alternative services.

### Treatment

#### Intervention

The multi-component strategy we have developed is comprised of four modules: screening and postal information, telephone counseling, an initial one-on-one interview, and case management. There are not any restrictions on concomitant care and interventions during the trial. Table 1 describes the four components of the multi-component strategy in line with the Template for Intervention Description and Replication (TIDieR) checklist [14].

**Table 1 Tab1:** Description of the four components according to the TIDieR checklist

Brief name	Postal information	Telephone counseling	Initial one-on-one interview	Case management
Why	Individuals are addressed personally with postal information. The individuals to be contacted are selected by means of a standardized and validated risk index [14]. This score enables sensitive and specific identification of persons who will receive a disability pension without additional intervention. The postal contact is intended to ensure that the selected individuals decide to call the case manager and participate in our case management intervention. In formulating the cover letter, we drew on the self-determination theory [15]. This theory assumes that individuals perform self-determined actions to satisfy their needs for competence, social inclusion, and autonomy. The persons contacted should feel competent to grasp the information through appropriate language. Their autonomy is confirmed, in that the offer is designated as a voluntary measure. The demand for social inclusion is met by the objective of equal participation that we have formulated. The better the cover letter can meet the three criteria, the more the individuals will be motivated to call the case managers. The cover letter also communicates that the three needs can be met as part of the intervention.	The telephone counseling session is intended to clarify all important questions regarding case management, data protection, confidentiality, and voluntariness. It should also pave the way for an initial interview. At the end of the initial telephone contact, the information provided should enable the person to decide whether case management is an option for him/her.	The person and the case manager get to know each other. During the initial interview, all further questions about case management, study participation, data protection, confidentiality and the voluntary nature of participation are clarified. The person should make an informed decision about participating in the case management intervention. The case manager should use the health, personal, and biographical information provided by the participant to develop initial ideas for possible services and support. Finally, the case manager needs to clarify the eligibility of the individual person for our model assessing some medical data.	Case management is a person-centered individual case intervention. We chose this approach to individually assess the multiple interactions of health problem, environment and person described in the model of the International Classification of Functioning, Disability, and Health [16] and to allow shared planning on how to improve the individual’s participation. The involvement of other stakeholders in the social environment recognizes that disability is also a social situation. To increase the likelihood that participants will achieve their goals, goals are formulated as specific, measurable, achievable, relevant, and time-bound. Coaching approaches are used to enhance the participant’s self-reflection skills, acceptance of illness, resilience, and motivation. A resource-based approach aims to activate available skills.
What (materials)	Personalized letters	Guideline for initial telephone contact and computerized documentation	Guideline for initial one-on-one interview; computerized documentation; questionnaire for the collection of medical data to check eligibility; study information; informed consent form (in duplicate); baseline questionnaire	Worksheet “Analysis of needs and agreement on objectives”; computerized documentation; toolbox with working materials on medical and vocational rehabilitation, rehabilitation aftercare, reintegration and job retention (graded return-to-work, company integration management, rights and obligations of the employer, degree of disability, and termination), reorientation and job acquisition (career orientation, job application training), health and therapeutic services, social security and support; follow-up questionnaire at the end of the case management intervention
What (procedures)	The selection of the persons to be contacted is made using a computerized algorithm that combines various characteristics stored in the individual accounts at the pension insurance institution (e.g., age and duration of receipt of sickness benefits and unemployment benefits) [6]. We applied weights when combining the various administrative data. Individuals with a risk index score of at least 60 points and who have received sickness benefits in the past year are contacted by the German Pension Insurance North.	The person contacted calls the case manager using the contact details provided in the personalized letter and is informed in a telephone counseling about the goals and implementation of the case management intervention. An initial one-on-one interview is arranged with the case manager.	The person meets with the case manager at an agreed upon location for an initial one-on-one interview.	Case management includes an initial phase of up to three appointments, a phase of individually tailored support and a final evaluation meeting. Intermediate assessment meetings are held at regular intervals to review and, if necessary, update needs and goals. Individualized assistance includes, among other things, consultations on health and social benefits, joint workplace meeting, support in applying for further services, acquisition of potential new employers or internships, coaching on reorientation and job applications, and educational and psychological interventions.
Who provided	German Pension Insurance North (provision of data and dispatch of information letters) and researchers (calculation of the risk index)	Case manager	Case manager	Case manager
How	Postal and individually	By phone and individually	In presence and individually	In presence and individually; if necessary, with the involvement of other stakeholders (e.g., employer, employee representatives, and company physician)
Where	German Pension Insurance North (provision of data and dispatch of information letters) and University of Lübeck (calculation of the risk index)	Workplace of the case manager	Residence of the person or agreed meeting place	Residence of the participant or agreed meeting place or workplace of the case manager; if necessary, other institutions (e.g., offices and counseling centers)
When and how much	Once per individual in several waves	Once after receiving the postal information and 10 to 15 min	Once after telephone counseling and 1 h	Up to 50 h within 1 year after initial interview and approval by the German Pension Insurance North; familiarization (two to three appointments); monitoring and interim review (every 3 months); final interview (one appointment)
Tailoring	Not planned	Not planned	Not planned	The elements individually tailored to the needs of the participants are derived from the jointly developed goals. The dose of case management is also individual. The upper limit is 50 h. Mandatory and regular interim meetings are held to structure the intervention. The toolbox outlined above, with its various working materials, supports the individual design of the case management intervention.
How well	The calculation of the risk index scores uses administrative data with high validity and is performed with a computer syntax. Sampling is described in a guideline to ensure standardized implementation.	The implementation of the telephone counseling is described in a guideline to ensure standardized implementation. The initial telephone contact is documented by the case manager in a standardized manner. To support the accuracy of the implementation, the telephone contacts are discussed with the researchers in bi-weekly video conferences.	The initial one-on-one interview is described in a guideline to ensure standardized implementation. The initial one-on-one interview is documented by the case manager in a standardized manner. To support the accuracy of the implementation, the interviews are discussed with the researchers in bi-weekly video conferences.	All processes that are mandatory in the case management intervention are described in guidelines to ensure standardized implementation (entry into case management, including needs analysis and goal finding, monitoring and final interview). The toolbox provides materials that can be used by the case managers to customize their approach. The case management is documented in a standardized manner to track the accuracy of the implementation of the guideline, as well as the frequency of use of the toolbox elements and contacts with participants and external institutions. Regular video conferences will be held to support accuracy of implementation throughout the process. At the end of the intervention, all case management participants are asked using standardized questionnaires which case management components they received during the intervention.

#### Control

The control group is identified in the same way as the intervention group but will be not informed about the case management intervention.

### Ancillary and post-trial care

Ancillary and post-trial care are not planned. Compensation for harms due to study participation is also not planned.

### Outcomes and other measures

#### Randomized controlled trial

A complete list of all measured constructs, measurement points and expected scaling of the randomized controlled trial can be found in Table 2. Adverse events will not be systematically assessed.

**Table 2 Tab2:** Measures, assessment, expected scaling, and measurement occasions in the randomized controlled trial and the nested observational study

*Outcome*	*Source and reference*	*Scaling*	*Baseline*	*End of the case management intervention*	*12-month follow-up*
**Primary outcome**					
Utilization of medical or vocational rehabilitation services	Administrative data from the individual pension insurance account	Binary			X
**Secondary outcomes**					
Employment	Administrative data from the individual pension insurance account	Continuous	X		X
Receipt of unemployment benefits	Administrative data from the individual pension insurance account	Continuous	X		X
Receipt of sickness benefits	Administrative data from the individual pension insurance account	Continuous	X		X
Disability pension	Administrative data from the individual pension insurance account	Binary	X		X
**Tertiary outcomes**					
Physician visits	Own development	Continuous	X^1^		X
Psychosocial health	HEALTH-49 [17]	Continuous	X^1^		X
Self-reported prognosis of employability	SPE [18]	Continuous	X^1^		X
Limitations on participation	IMET [19]	Continuous	X^1^		X
Health state	EQ-5D-5L [20]	Continuous	X^1^		X
Perceived stress	PSS-10 [21]	Continuous	X^1^		X
Social support	F-SozU K-6 [22]	Continuous	X^1^		X
Life satisfaction	SOEP [23]	Continuous	X^1^		X
Information about services supporting participation	Own development	Continuous	X^1^	X^2^	X
Work participation	Own development	Binary	X^1^	X^2^	X
Sick leave duration in weeks	Own development	Continuous	X^1^		X
Work ability	WAS [24]	Continuous	X^1^		X
Sociodemographic data	Own development	Nominal/continuous	X^1^	X^2^	X
Dose delivered: telephone counseling	Computerized sheet (own development)	Binary/continuous		X^2^	
Dose delivered: one-on-one interview	Computerized sheet (own development)	Binary/continuous		X^2^	
Dose delivered: case management	Computerized sheet (own development)	Binary/continuous		X^2^	
Initiated services	Own development	Binary		X^2^	
Needs assessment	Own development	Continuous		X^2^	
Relationship with case manager	Own development	Continuous		X^2^	
Competence of case manager	Own development	Continuous		X^2^	
Goal attainment	Own development	Continuous		X^2^	
Content of case management	Own development	Continuous		X^2^	
Rating of case management components	Own development	Continuous		X^2^	

*EQ-5D-5L* 5-level EQ-5D, *F-SozU K-6* 6-item brief form of the Perceived Social Support Questionnaire (Fragebogen zur Sozialen Unterstützung), *HEALTH-49* Hamburg modules for the assessment of general aspects of psychosocial health for therapeutic practice (Hamburger Module zur Erfassung allgemeiner Aspekte psychosozialer Gesundheit für die therapeutische Praxis), *IMET* Index for the measurement of limitations of participation (Index zur Messung von Einschränkungen der Teilhabe), *PSS-10* Perceived Stress Scale, *SOEP* Socio-Economic Panel, *SPE* Self-reported prognosis of employability, *WAS* Work Ability Score

^1^ randomized controlled trial and observational study; ^2^ observational study only

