**Assessments**				
Baseline questionnaire		X		
Questionnaire at the end of the case management intervention			X	
12-month follow-up questionnaire				X
Computerized documentation by case managers		Continously		

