### Data collection

Outcomes are collected using administrative data from the German Pension Insurance North, patient questionnaires and computerized documentation by case managers (Tables 2 and 3). The administrative data capture our primary and secondary outcomes of the randomized controlled trial completely, reliably, and validly for both the intervention and control group participants. These data are transmitted electronically, encrypted and pseudonymized by the German Pension Insurance North to the University of Lübeck. The patient questionnaire to assess tertiary outcomes of the randomized controlled trial will be sent out 12 months after random assignment by the German Pension Insurance North with a return envelope addressed to the University of Lübeck. The questionnaires of the observational study are handed out to the participants by the case managers and returned to them completed or handed out together with a return envelope addressed to the University of Lübeck. The computerized case manager documentation was developed with the case managers to ensure the feasibility of the documentation, and all case managers were trained on the required documentation before the randomized controlled trials began. Case managers send their computerized documentation of the telephone counseling, the one-on-one interview, and the case management intervention weekly to the researchers, who check it for completeness and validity. The patient forms and computerized documentation of the case managers were tested in a previous pilot study. If participants withdraw their consent, the collected data will be deleted.

The use of administrative data will ensure complete coverage of primary and secondary outcomes from all study participants. Moreover, we created a website to transparently inform study participants about the study and to maintain interest in the study. Three weeks after the first mailing of the 12-month follow-up questionnaire a single reminder is sent, again containing the questionnaire and the return envelope addressed to the University of Lübeck.

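### Table 2 attributes a questionnaire baseline to the randomised trial, but that questionnaire reaches only intervention-arm interviewees and no controls

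*Protocol article*

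**What the plan says.** The article introduces Table 2 as the full list of constructs and measurement points of the randomised trial. Among the tertiary outcomes, 13 rows carry footnote 1 on the Baseline cell: physician visits, HEALTH-49, SPE, IMET, EQ-5D-5L, PSS-10, social support, life satisfaction, information about services, work participation, sick leave duration, work ability and sociodemographic data. Footnote 1 reads "randomized controlled trial and observational study". The 12-month cells of these rows carry no footnote. Footnote 2, used elsewhere in the table, marks cells that belong to the observational study alone.

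Other sections describe how the questionnaires reach people:

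- Table 1, materials for the initial one-on-one interview: "study information; informed consent form (in duplicate); baseline questionnaire".
- Table 3: randomisation is in the pre-intervention column; the row "Baseline questionnaire" is marked only at the beginning of the intervention.
- Data collection, on the observational study: "The questionnaires of the observational study are handed out to the participants by the case managers". The trial's tertiary questionnaire "will be sent out 12 months after random assignment by the German Pension Insurance North".
- Trial design: "Only the intervention group is informed about the possibility of our case management intervention". Later, "all individuals will be contacted by the German Pension Insurance North 1 year after random assignment, informed about the study".
- Blinding: controls learn their assignment only when asked to complete the tertiary questionnaires.

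Statistical methods gives linear regression for continuous tertiary outcomes and multiple imputation for incomplete 12-month responses. It attaches baseline adjustment only to the Poisson models of the continuous secondary outcomes.

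**The concern.** Read as printed, Table 2 tells an analyst that the randomised trial holds baseline scores for its patient-reported outcomes. An analyst who believes this could adjust the tertiary regressions for those scores, form change scores, or add them to the imputation model.

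If the other sections are right, the scores are absent by design for every control. They exist only for intervention participants who chose to telephone and then attended an interview. They are also recorded after randomisation, and after the letter and the telephone counselling. They are therefore not a baseline for the randomised comparison. Using them there would either restrict the comparison to a self-selected group in one arm or rest it on imputed values that no control observation can inform. What is at stake is the validity of the randomised tertiary comparisons, should the scores be used in them.

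**Working it through.** **1. Can any control receive the baseline questionnaire?** The passages on delivery agree with one another.

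- Table 1 ties the questionnaire to the interview, the third module of the intervention.
- Table 3 schedules it after randomisation.
- Data collection gives two routes only: case managers for the observational study, and a posted questionnaire at 12 months for the trial.
- Trial design and Blinding leave controls unaware of the study until that posting.

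No route reaches a control at baseline. Footnote 1 is the only text that says otherwise.

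**2. Could footnote 1 mean only that the construct is used in both studies?** The footnotes are attached to individual cells, not to row labels. Work participation, for example, has footnote 1 at baseline, footnote 2 at the end of case management and none at 12 months. The observational-study label was available and was not used on the Baseline cells. As printed, footnote 1 is a statement about the baseline measurement.

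**3. How many baseline questionnaires are expected?** Inputs from Sample size: 4500 in the intervention arm, 12.5% contact a case manager, half of those attend the interview, and 80% of those start case management.

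- Contacts: 4500 × 0.125 = 562.5
- Interviews: 562.5 × 0.5 = 281.25, about 281
- Case management starts: 281.25 × 0.8 = 225

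The last figure reproduces the 225 targeted in Recruitment.

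| Group | Expected with baseline questionnaire | Share |
|---|---|---|
| Intervention arm, interviewed | 281 of 4500 | 6.25% |
| Intervention arm, starting case management | 225 of 4500 | 5% |
| Control arm | 0 of 4500 | 0% |
| All randomised, interviewed | 281 of 9000 | 3.1% |
| All randomised, starting case management | 225 of 9000 | 2.5% |

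With 281 questionnaires, the score would be missing for 9000 − 281 = 8719 people, or 8719/9000 = 96.9% of those randomised.

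**4. Does a stated analysis use these scores?** No. The tertiary regressions are named without baseline adjustment, and the imputation is described without naming predictors. The start-to-end tests (paired t and McNemar) are confined to case management participants, for whom the interview questionnaire is the proper baseline.

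**5. Which baselines do both arms have?** Table 2 lists administrative baseline values for employment, unemployment benefits, sickness benefits and disability pension. Age and gender come from records. The risk index, and the income and benefit data behind it, are computed before randomisation.

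**The case against.** The strongest reply is that this is a labelling slip with no consequence in the stated plan. The data flow is clear from the other sections. Baseline adjustment is reserved for administrative outcomes, and change over time is analysed only within the observational study. Most misuse would also reveal itself: a complete-case model adjusted for baseline, or a change-score comparison, would contain no controls and could not estimate an arm effect. Only an imputation model could absorb the scores unnoticed, and the article specifies no such model. Covariate lists and imputation predictors are usually left to the analysis plan.

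Much of this stands. A reader might infer that the planned tertiary analysis is biased or departs from intention-to-treat. The document does not support that, because no stated model uses the scores. Nor does it support saying that no baseline exists between the arms, since administrative baselines do. The absence of control questionnaires at baseline follows from the Zelen design and is not itself a defect. The figure of 281 is an expectation from assumed uptake, not a ceiling.

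What does not stand is that the slip can be left alone. Table 2 is offered as the complete list of measurement points, and on 13 rows it reports a trial measurement that the design does not make.

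**Conclusion.** The contradiction holds. Footnote 1 gives the randomised trial a questionnaire baseline that Trial design, Table 1, Table 3, Blinding and Data collection together rule out. Under the protocol's uptake assumptions, about 6% of the intervention arm and none of the controls would have it; higher or lower uptake would change the first figure but not the second.

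The scope is limited to questionnaire measures, hence to tertiary outcomes. The primary and secondary outcomes, the sample size and the stated models are untouched. Bias is conditional: it would arise only if the interview scores entered the randomised tertiary regressions or the imputation. The point should be corrected before analysis, but it does not undermine the trial. The correction is also an opportunity to say that pre-randomisation administrative data, already held for everyone, can serve the purpose that questionnaire baselines cannot. How much precision this would add depends on correlations that the article does not report.

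**What to change.** 1. In Table 2, change the Baseline cells of the 13 rows from footnote 1 to footnote 2, so that they are assigned to the observational study alone, and mark the 12-month cells as the randomised trial's measurement.
2. In Statistical methods, state that randomised comparisons of tertiary outcomes are between-arm comparisons of 12-month values.
3. State that the regression and imputation models for these comparisons draw on pre-randomisation administrative variables held for both arms, and that the interview baseline questionnaire is not used in either. Suitable examples are age, gender, risk index, prior benefit and employment data, and cohort (2021 or 2022). The final list can be left to the analysis plan.

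The cost is a footnote edit, a sentence or two and slightly more analysis work. No new data are collected and the design does not change.
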